## Vital Signs, SpO2 and Complete Physical Examination

The subjects will examine the vital signs and SpO2, and perform a complete physical examination at the time points in the study flow chart. Vital signs should be measured after the subject rests for at least 5 minutes. Blood pressure should be measured with the dominant arm at the same height as the heart in a sitting position.

## 12-Lead ECG

The subjects will undergo a 12-lead ECG at the time points in the study flow chart. It is required to be performed after the subject rests quietly for at least 5 minutes. The ECG examination should at least include: heart rate, PR, QT and QTc intervals. If QTc interval increases > 30 ms from pre-dose, up to 2 ECGs will be added with at least 10 minutes apart to determine the

accuracy of the original measurement and exclude abnormal ECGs due to incorrect lead placement.

### **Use of antiemetics**

The use of antiemetics will be recorded from the end of surgery to the end of the follow-up period.

### **PK Evaluation**

Blood samples will be collected from subjects at the study site according to the time points in the study flow chart. The biological sample testing unit will analyze the plasma SHR8554 concentration (the test substances will be ultimately decided according to the Method Validation Report) and the genetic testing unit will analyze the gene of drug metabolizing enzymes.

### **Collection and processing of PK blood samples**

PK blood samples will be collected according to the protocol requirements, and 3 mL of venous blood samples will be collected into K2EDTA tubes (in case of indwelling needle, about 0.5-1 mL of blood should be drawn and discarded before each blood collection, and the tubes will be sealed with heparin sodium or normal saline after collection is completed). Centrifuge for 10 min (centrifugal force 1500 g) at 2-8 °C within 2 h to obtain clear upper plasma (if the effect of separating plasma from blood cells is not good under this condition, the centrifuge can be adjusted appropriately, but the maximum centrifugal force should not exceed 2500 g). After centrifugation, a minimum of 0.5 mL of upper plasma will be transferred into a cryogenic cryovial (test sample), and the remaining plasma will be transferred to another vial as backup sample. The remaining lower blood cell samples after plasma removal will be stored in blood collection tubes (subjects who consent genetic testing will store the lower blood cell samples at two time points). The duration from the end of centrifugation until plasma separated and frozen in a freezer should be no more than 1 h. The duration from whole blood collection until plasma separated and frozen in a freezer should be no more than 2 h. The test plasma samples, backup plasma samples and lower blood cell samples will be stored upright in a freezer below -60 °C, until transport. See *Clinical Sample Operation Manual* for the specific operation.

Each sample has a unique sample number. The test plasma samples will be stored on dry ice and sent to the sample analysis laboratory, while the backup plasma samples will be stored at the clinical unit or at the sponsor-designated unit. Lower blood cell samples will be stored on dry ice and sent to the genetic testing unit.

The actual date and time of blood sample collection and the exact time of treatment will be recorded in the PK blood sample collection page of the study medical record and eCRF.

Problems encountered in the collection of blood samples will be noted in the study medical record and eCRF.

## **Adverse Events Reporting**

### **Adverse Events (AEs)**

#### **Definitions of Adverse Events**

Adverse event (AE) is defined as any untoward medical condition that occurs after a subject receives the drug, which may manifest as symptoms, signs, diseases, or laboratory abnormalities, but does not necessarily have a causal relationship with the investigational product. AEs include, but are not limited to, the following:

- 1) Worsening of pre-existing (before enrollment) medical conditions/diseases (including worsening of symptoms, signs, laboratory abnormalities);
- 2) Any new AEs: any new adverse medical conditions (including symptoms, signs, newly diagnosed diseases);
- 3) Abnormal and clinically significant laboratory values or results.

The study personnel should record in detail any AE, including: AE name, time of onset, severity, relationship to the investigational product, end time, action taken with the investigational product, and final results and outcome.

AE information will be collected from the time the subject signs the ICF until the end of the safety follow-up period. Physical conditions (including laboratory abnormalities) that are already present at the time of the subject's screening examination (including those newly identified at the time of the screening examination) will be recorded as pre-existing or concomitant diseases and will not be recorded as AEs. However, if a pre-existing or concomitant condition worsens during the study, an AE should be recorded.

Surgeries/treatments scheduled prior to informed consent but to be conducted during the study, or planned hospitalizations, or surgery-related events (e.g., post-operative diagnoses [including polyps, inflammation, tumors, etc.], biopsy results, etc.) will not be recorded as AE.

#### **Adverse Event Severity and Grading Criteria**

Mild, moderate, and severe will be used to describe the extent of adverse events. The severity will be graded according to the following uniform criteria:

- Grade 1 (mild): usually transient, generally does not affect activities of daily living, does not require medical treatment, or may require minimal treatment;
- Grade 2 (moderate): the subject feels unwell, his/her activities of daily living are affected, and usually requires treatment to mitigate, but there is no risk of major or permanent harm to the

subject;

- Grade 3 (severe): the subject's activities of daily living are interrupted, or the clinical condition is seriously affected, and centralized treatment and intervention are required;

Note that the severity and seriousness of AEs should be differentiated. Severe is only used to describe the extent, for example, headache may be severe in intensity, but cannot be listed as a serious adverse event (SAE) unless it meets the SAE criteria as described in **Section 8.2.1**.

### **Relationship of Adverse Events to the Investigational Product**

Any untoward reactions or abnormal changes in objective laboratory indicators reported by the subject during treatment should be truthfully recorded, and the AE manifestations, severity, duration, treatment and outcome should be indicated. The investigator should comprehensively determine the relationship between the AE and the investigational product, such as whether the AE has a reasonable temporal relationship with the treatment, characteristics of the investigational drug, the toxicological and pharmacological effects of the investigational drug, whether the subject uses other concomitant drugs, the subject's underlying disease, medical history, family history, challenge and rechallenge reactions, etc. The possible relationship between AEs and the investigational product will be assessed according to the five-level classification of "related, possibly related, unlikely related, unrelated, and not determined".

### **Serious Adverse Events (SAEs)**

#### **Definition of SAE**

Serious adverse event (SAE) is an event that occurs during the clinical trial that requires hospitalization or prolonged hospitalization, leads to disability or incapacity, is life-threatening or fatal, or results in congenital malformations. SAEs include the following medical events:

- Fatal;
- Life-threatening: defined as the subject is at the risk of death at the time of the event rather than assuming a possible death if the condition worsens;
- Requires hospitalization or prolonged hospitalization;
- Leading to permanent or serious disability/incapacity;
- Resulting in congenital anomalies/birth defects;
- Other medically significant events (defined as adverse events that may not immediately result in death, be life-threatening, or require hospitalization, but may jeopardize the subject or require intervention to prevent any of the above outcomes. For example, allergic bronchospasm requiring special treatment in an emergency room or at home, dyscrasia or convulsions that do not result in hospitalization, or development of drug dependence or drug abuse).

## **Hospitalization**

AEs in clinical studies that lead to hospitalization (even if less than 24 hours) or prolonged hospitalization should be considered as SAEs.

Hospitalization does not include the following:

- Hospitalization for this abdominal operation
- Admission to rehabilitation facilities
- Admission to nursing homes
- Admission to routine emergency room
- Day surgery (such as outpatient/day/ambulatory surgery)

Any hospitalization or prolonged hospitalization due to any causes other than AE deterioration will not be considered as a SAE. For example, the following reasons are not considered as SAEs:

- Hospitalization for a pre-existing disease that does not worsen without any new AEs (e.g., hospitalization due to laboratory abnormalities that occur prior to the study and still persist);
- Hospitalization due to administrative reasons (e.g., annual routine physical examination);
- On-study hospitalization as specified in the protocol (e.g., protocol-specified procedures);
- Elective hospitalization for any cause other than worsened AEs (e.g., elective surgery);
- Pre-scheduled treatment or surgical procedures (recorded in the protocol and/or in the subject's individual baseline data);
- Hospitalization only for use of blood products.

Any diagnostic or therapeutic invasive (e.g., surgery) or non-invasive procedure should not be reported as an AE. However, the condition that results in such procedures should be reported as an AE if it meets the criteria of AE. For example, acute appendicitis that occurs during the AE reporting period should be reported as an AE, while the appendectomy thus performed should be recorded as the treatment of the AE.

## **Pregnancy**

If a female subject becomes pregnant during the clinical study, the subject will be discharged from the study; if the partner of a male subject becomes pregnant during the clinical study, the subject will continue the clinical study. The investigator should fill the Hengrui Clinical Study Pregnancy Report/Follow-up Form and report it to the sponsor within 24 hours after becoming aware of the pregnancy event.

The investigator should follow up the pregnancy event to the final outcome (including any

premature termination of pregnancy or delivery), and follow up the delivery until 1 month after delivery. The pregnancy results should be reported to the sponsor. If the pregnancy results meet the criteria for an SAE (eg, extrauterine pregnancy, spontaneous abortion, intrauterine fetal death, death neonatal, or congenital anomaly, etc.), then it should be reported following the procedures of SAE reporting.

If a subject experiences an SAE during pregnancy, the SAE reporting procedure should also be followed.

## **Reporting Procedures**

### **Serious Adverse Event Reporting**

The collection period of SAEs should start from signing the ICF until the end of the safety follow-up period. In the event of an SAE, whether the initial report or the follow-up report, the investigator must immediately fill in the Clinical Study Serious Adverse Event/Adverse Event of Special Interest Report Form, sign and date, notify the sponsor immediately within 24 hours after becoming aware of it, and promptly report it to relevant institutions in accordance with local regulatory requirements.

SAEs that occur after the safety follow-up period but are suspected to be related to the investigational product should be collected. For SAEs, the symptoms, severity, relationship to the investigational product, time of occurrence, time of management, measures taken, follow-up time and manner, and outcome should be recorded in detail. If the investigator thinks that an SAE is unrelated to the investigational product but potentially related to the study conditions (e.g., termination of the pre-existing treatment, or complications during the trial), it should be described in the narrative section of the SAE report. If the severity of an ongoing SAE or its relationship to the investigational product is changed, a follow-up report should be submitted immediately. False information included in the previous SAE report per the investigator may be corrected, revoked or downgraded in the follow-up report, and reported in accordance with the SAE reporting procedures.

The sponsor of this project receives SAE (and pregnancy) reports at: [[name]](mailto:[contact]).

### **Follow-up of AEs/SAEs/Pregnancies**

At each study visit, the investigator should assess whether the subject experiences an AE. All AEs/SAEs should be followed until the event disappears, resolves to baseline, stabilizes, or is reasonably explained (eg, lost to follow-up or death). Every effort should be made to ensure that the subject gets the best outcome and a clear causality assessment. The principles of collection and follow-up period of AEs/SAEs occurring in the study can be found in Table 8-1.

**Table 8-1 Principles of AE/SAE/Pregnancy Collection and Follow-up Period**

| Interval                                          | Collection Requirements                                                                                   |
|---------------------------------------------------|-----------------------------------------------------------------------------------------------------------|
| Signing the ICF to end of safety follow-up period | All AEs/SAEs
* Pregnancy events (start the collection after the first dose of investigational product) |
| After the safety follow-up period                 | Drug-related SAEs                                                                                         |

### **Clinical Monitoring**

Clinical monitoring of the study site is required to ensure that the subject's rights and interests are protected, the reported study data are accurate, complete and reliable, and the study is conducted in accordance with the currently approved protocol/amended protocol, Chinese GCP, and applicable regulatory requirements.

### **Data Analysis/Statistical Method**

#### **Sample Size**

With reference to the results of the foreign study TRV130-3002, assuming that the primary efficacy variable SPID24 in the SHR8554 0.75 mg group in this study is comparable to the efficacy in the 0.35 mg group in the TRV130-3002 study, and conservatively assuming that the mean (standard deviation) of SPID24 in the low dose group of this study is 88 (45), and the mean (standard deviation) of SPID24 in the placebo group is 70 (40), it's estimated to need 118 subjects in each group by the sample size calculation formula (PASS) of comparing the means of two samples to achieve the power of 90% with  $\alpha = 0.05$  (two-sided), provided that the four groups are designed in a 1:1:1:1 ratio. Considering the dropout rate of 10%, each group is planned to enroll 132 subjects, with a total of 528 subjects.

#### **Statistical Analysis Plan**

The detailed methods for summarization and statistical analysis of the data collected for this study will be included in the SAP which will be finalized and filed prior to database lock. If a change is made to the protocol that will have an important impact on the SAP per the sponsor or the principal investigator and statistician, the SAP should be revised to be consistent with the protocol.

## Statistical Hypotheses and Discriminant Rules

The primary efficacy variable of this trial is SPID24, and the difference test will be used for the group comparison between the experimental group and the placebo group.

Hypothesis:

$$H_0: \mu_T = \mu_C$$

$$H_1: \mu_T \neq \mu_C$$

$\alpha$  level: 0.05 (two-sided).

In this study, the high and low dose groups will be tested sequentially to ensure that the Type I error rate  $\alpha$  is controlled within 0.05 (two-sided). The test between the high dose group and the placebo group will be performed first with  $\alpha$  of 0.05 (two-sided). If there is a significant difference between the high dose group and the placebo group, then the test between the low dose group and the placebo group will be performed with  $\alpha$  of 0.05 (two-sided); if there is no significant difference between the high dose group and the placebo group, only exploratory analysis will be performed for the comparison of the low dose group and the placebo group. For the morphine group, only descriptive statistics will be applied.

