| Data Analysis / Statistical Methods | 
The general principles for descriptive statistical analysis in this study are as follows: Count data will be summarized using frequencies and percentages. Measurement data will be summarized using mean, standard deviation, median, maximum, minimum, etc. Plasma concentration data will be summarized using mean or geometric mean, standard deviation, coefficient of variation or geometric coefficient of variation, median, maximum, and minimum. SAS 9.4 will be used for calculation, and all statistical tests will be performed using two-sided tests, with <math>P \leq 0.05</math> considered as statistically significant.
 
Efficacy Analysis
 
The primary efficacy variable SPID24 will be compared between groups using analysis of variance, and SPID24 in each group will be statistically described. The high dose group and low dose group will be tested sequentially, and descriptive statistics will be performed in the morphine group. For the secondary efficacy variables, analysis of variance, chi-square test, Fisher's exact probability method, and nonparametric test will be used for difference analysis according to the nature of the data.
 
Safety Analysis
 |

|  |                                                                                                                                                                                                                                                                                                                                              |
|--|----------------------------------------------------------------------------------------------------------------------------------------------------------------------------------------------------------------------------------------------------------------------------------------------------------------------------------------------|
|  | 
The incidence of AEs and ADRs in each group will be compared using chi-square test or Fisher's exact probability method, and frequency and percentage will be used to describe the AEs and ADRs.
 
PK Analysis
 
The population PK model parameters (CL, V, etc.) will be estimated using the pharmacometric method.
 |

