### **Selection of Control Drug**

In 2007, the Center for Drug Evaluation (CDE) of the National Medical Products Administration issued "Key Points to Consider in Clinical Trials for Analgesic Drug Registration in China", which states: "Randomized controlled studies comparing with placebo are required". A placebo control will be used to investigate the true adverse events of the investigational product and to compare the efficacy of the investigational product with that of placebo. The analgesic effect of morphine is clear, so it is used as a positive control to compare with the safety and efficacy of the investigational drug.

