### **Safety Analysis**

Safety analysis will be tabulated and analyzed by descriptive statistics based on the Safety Set (SS), including AEs, laboratory tests, vital signs, electrocardiogram data, etc.

AEs will be coded according to MedDRA. AEs will be summarized by treatment group. The incidences of AEs, drug-related ADRs, SAEs, etc. will be summarized by system organ class (SOC) and preferred term (PT), and relevant adverse events will be tabulated. Incidences (number of subjects: number of subjects with at least one AE) will be calculated by SOC and PT; if a subject experiences the same AE for many times, the AE with the highest severity will be counted.

Other safety variables will be summarized using descriptive statistics. The mean, standard deviation, maximum, minimum and median will be used to describe each measurement and change from baseline. The frequency and percentage will be used to describe categorical

variables.

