#### 4.2 Treatment-related Adverse Events

The investigator should comprehensively assess and judge the relationship between the AE and the investigational product according to the five-level classification of "related, possibly related, unlikely related, unrelated, not determined". "Related", "possibly related" and "not determined" adverse events are listed as treatment-related adverse events (TRAEs), the sum of which will be the numerator to calculate the incidence of TRAEs, while the number of all subjects for safety evaluation is the denominator.

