### 7.4.2 Adverse Events

TEAEs will be coded according to the current version of MedDRA at the time of coding and processed in the statistical analysis.

- The number and incidence of treatment-emergent adverse events/treatment-related adverse events, treatment-emergent serious adverse events/treatment-related serious adverse events, and adverse events leading to withdrawal from the study/treatment-related adverse events will be summarized by SOC and PT;
- Treatment-emergent adverse events/treatment-related adverse events occurring in  $\geq 10\%$ / $\geq 5\%$  of subjects ( $\geq 10\%$ / $\geq 5\%$  in any group) will be summarized by PT;
- The number and incidence of adverse events of special interest, i.e., nausea, vomiting, dizziness, respiratory depression (respiratory depression defined as respiratory rate  $< 8$  beats/min and/or oxygen saturation  $< 90\%$ ) during the treatment period, will be summarized;

If a subject experiences multiple AEs, he/she will be counted only once in incidence calculation; if a subject experiences the same AE for multiple times, he/she will be counted only once in the incidence calculation of this AE.

AEs will be summarized in frequency tables by system organ class (SOC) and preferred term (PT). Incidence (number of subjects: number of subjects with at least one AE) will

be calculated by system and symptom/sign.

The number and incidence will be calculated by severity and relationship to study drug, SOC and PT, respectively (for AEs with repeated occurrences, the event with the worst severity will be calculated for analysis).

A listing of all AEs and SAEs experienced by the subjects will be provided.

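### SAP 4.2 counts events where an incidence needs subjects, the synopsis and the body disagree on whether adverse event rates are tested, and no estimate against morphine is specified

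*Combined protocol and SAP*

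**What the plan says.** **TRAE incidence.** SAP 4.2 groups events judged related, possibly related or not determined as TRAEs, "the sum of which will be the numerator to calculate the incidence of TRAEs", with all subjects evaluated for safety as the denominator. SAP 7.4.2, which specifies the TRAE tables, says that a subject with several events is one case: "he/she will be counted only once in incidence calculation". It defines incidence by subjects with at least one event. The protocol's Safety Analysis section (10.5) gives the same subject-based definition.

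**Comparison of adverse event rates.** The synopsis states: "The incidence of AEs and ADRs in each group will be compared using chi-square test or Fisher's exact probability method". It names no pairs of groups and makes no exception for morphine. Protocol 10.5 describes the safety analysis as descriptive, and SAP 7.4.2 contains no test. SAP 2.8 records no change to the protocol's statistical analysis.

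**Morphine.** Under Selection of Control Drug the protocol says that morphine's analgesic effect is clear, "so it is used as a positive control to compare with the safety and efficacy of the investigational drug". Protocol 10.3 then states "For the morphine group, only descriptive statistics will be applied", and SAP 7.1.2 repeats this. The test sequence in SAP 7.3.1 is high dose against placebo, then low dose against placebo, with a difference and 95% CI. The secondary endpoints in SAP 7.3.2 refer to sequential tests as well.

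**The concern.** A numerator of events over a denominator of subjects is not a proportion. It can exceed 100%, and it depends on how often events recur within a subject, so it can order the arms differently from a count of affected subjects. A programmer working from SAP 4.2 and one working from SAP 7.4.2 would produce different tables under the same label.

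The split between the synopsis and the body leaves open whether p-values for adverse events will be produced and for which pairs. That choice should not be made after unblinding.

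The morphine arm is a quarter of the trial (132 of 528), and its stated purpose has no prespecified estimate. Two questions depend on it. If SHR8554 does not separate from placebo, was the drug ineffective, or was the trial unable to detect an effective analgesic? And how does SHR8554 compare with a classic opioid on nausea, vomiting, dizziness and respiratory depression, the four events that the plan singles out? The first is not idle: in 201P, with about ten subjects per arm, 60% on morphine and 40% on placebo needed no rescue, a difference that was not significant. So small a study says little either way.

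**Working it through.** **1. The plan's own figure.** Inputs from protocol 10.1: SPID24 mean (SD) of 88 (45) for the low dose and 70 (40) for placebo, two-sided alpha 0.05, power 90%, dropout 10%.

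- Pooled SD = √((45² + 40²)/2) = 42.57; difference = 18.
- n = 2 × (1.960 + 1.282)² × 42.57² / 18² = 117.6, so 118 per group.
- 118/0.9 = 131.1, so 132 per group; 4 × 132 = 528.

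The stated 118, 132 and 528 reproduce. Morphine does not enter the calculation.

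**2. TRAE incidence under the two rules.** Inputs: the drug-related events and affected subjects reported for 201P in the protocol's background section.

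| Arm | Events | Subjects affected / N | SAP 4.2: events/N | SAP 7.4.2: subjects/N |
|---|---|---|---|---|
| 0.5 mg | 5 | 4/10 | 50% | 40% |
| 0.75 mg | 14 | 5/10 | 140% | 50% |
| 1.0 mg | 13 | 7/10 | 130% | 70% |
| Morphine | 17 | 7/11 | 154.5% | 63.6% |
| Placebo | 14 | 8/10 | 140% | 80% |
| All | 63 | 31/51 | 123.5% | 60.8% |

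The 201P report used the last column: it gives 60.78% overall. By events 0.75 mg equals placebo; by subjects it is 30 points lower. The 1.0 mg and morphine arms change order, but by subjects that is 7/10 against 7/11, one subject's difference in the denominator. The 0.75 mg and morphine arms keep their order.

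**3. Precision of contrasts with morphine at 132 per arm.** The documents give no morphine SD for SPID24 and no expected phase 3 adverse event rates, so both are assumed and shown as ranges.

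SPID24 half-width = 1.96 × √((s₁² + s₂²)/132):

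- SDs 40 and 40: 9.7
- SDs 45 and 40: 10.3
- SDs 45 and 45: 10.9

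Adverse event risk difference, common rate p, half-width = 1.96 × √(2p(1 − p)/132):

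- p = 20%: 9.7 points
- p = 30%: 11.1 points
- p = 50%: 12.1 points
- p = 60%: 11.8 points

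If only 118 per arm contribute, the ranges become 10.2 to 11.5 SPID24 units and 10.2 to 12.8 points. For scale, from an assumed morphine rate of 50% with 132 per arm, power is 37% for a 10-point reduction, 70% for 15 points and 92% for 20 points. These contrasts would therefore be informative estimates, not powered tests of modest safety differences.

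**The case against.** The best defence is that the working rules are sound and that morphine was deliberately left untested. Protocol 10.5, SAP 7.4.2 and the 201P report all count subjects, so the 124% would appear only if 4.2 were followed and the others ignored. The efficacy limitation on morphine is stated consistently in the synopsis, protocol 10.3 and SAP 7.1.2. The study objective makes no claim relative to morphine, and the protocol's remark about fewer side effects is framed as a matter of mechanism.

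Much of this stands, and it rules out several stronger readings.

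- A reader might infer that nothing is compared with morphine. The synopsis sentence on adverse events does not except that arm; the defect is that it conflicts with the body.
- A reader might infer that TRAE incidence rests on event counts throughout. It does so in SAP 4.2 only.
- A reader might infer that assay sensitivity and relative safety cannot be read from the output. The SAP reports n, mean and SD of SPID24, the rescue-free proportion with a Clopper-Pearson interval, and adverse event incidence for each arm. Unadjusted contrasts can be derived from these; they are just not prespecified.
- A reader might take the change of order between 1.0 mg and morphine as a safety signal. At 7/10 against 7/11 it is noise, useful only to show that the two rules can disagree.

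The defence does not dispose of the contradictions: SAP 4.2 still conflicts with 7.4.2, and the synopsis with protocol 10.5. The latter conflict lies mainly inside the protocol, since the SAP follows the body.

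**Conclusion.** There are three findings of different weight.

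1. SAP 4.2 is wrong as written. On the 201P counts its rule gives 124% instead of 60.8%. This needs no assumption beyond the protocol's own counts.
2. The synopsis and the body of the plan disagree on whether adverse event incidence is tested. They must be reconciled.
3. Specifying contrasts with morphine is a cheap improvement, not the repair of an invalid analysis. The stated purpose of the arm is comparison, and the data will exist. The expected half-widths are about 9.7 to 10.9 SPID24 units and 10 to 12 percentage points at 132 per arm, on the assumed SDs and rates above.

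It might be inferred that the primary conclusion is at risk. It is not: the primary analysis tests a difference from placebo, and a positive result there does not depend on morphine. The morphine-placebo contrast matters mainly if the doses fail, and the dose-morphine contrasts matter if relative efficacy or safety is to be discussed.

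**What to change.** - **SAP 4.2:** define the numerator as the number of subjects with at least one TRAE, in line with SAP 7.4.2 and protocol 10.5. If event counts are wanted, report them in a separate column that is not labelled incidence. This is one sentence.
- **Synopsis, protocol 10.5 and SAP 7.4.2:** state once whether adverse event incidence is tested. If so, name the pairs and the events and carry the tests into the SAP; if not, remove the test from the synopsis. Record any departure from the protocol in SAP 2.8.
- **SAP 7.3 and 7.4:** add, as descriptive estimates outside the alpha sequence, SPID24 differences with 95% CI for morphine minus placebo and for each dose minus morphine. Add risk differences with 95% CI for nausea, vomiting, dizziness and respiratory depression, for each dose against morphine and against placebo, using an interval method suited to small counts if an event is rare. Amend the descriptive-only sentence in protocol 10.3 and SAP 7.1.2 to allow these.

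The cost is a few tables and some wording. The downside is a set of intervals unadjusted for multiplicity, which must be labelled as such and must not support claims of superiority or equivalence to morphine.
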